#### 4. Study Interventions

Before sedation/analgesia for gastrointestinal endoscopy, all participants will undergo preoperative evaluation at the anesthesia clinic. Baseline data will be collected, including age, gender, height, weight, ASA classification, Mallampati classification, drinking history, surgical history, comorbidities (hypertension, diabetes, cerebrovascular disease, cardiovascular disease, liver and kidney diseases), and PRODIGY score [7]. Patients will be fasting for 6 hours and no fluids for 2 hours before the procedure. Upon entering the operating room, patients will be positioned according to the type of examination, and monitoring devices will be connected to record baseline vital signs

(non-invasive blood pressure, oxygen saturation, ECG, end-tidal carbon dioxide). Preoxygenation with an endoscopic mask (8-10 L/min, 3-5 min) will be performed under spontaneous breathing, and intravenous access will be established. Resuscitation drugs such as epinephrine, atropine, ephedrine, and phenylephrine will be prepared.

The anesthesia nursing staff will prepare the sedation/analgesia drugs according to the group assignment. Remimazolam tosylate (RT) will be diluted with normal saline to 1.25 mg/mL, and individualized dosing will be administered based on patient weight. All patients will receive lidocaine gel for pharyngeal surface anesthesia before undergoing gastroscopy. Oxygen will be administered via an endoscopic mask at 6 L/min from the start of the endoscopic procedure until the patient is fully awake. According to the expert consensus on sedation/analgesia for gastrointestinal endoscopy, remimazolam will be administered as a single intravenous (IV) bolus over 1 minute using a micro-infusion pump. The initial loading dose of remimazolam will be 0.15 mg/kg, combined with etomidate 0.1 mg/kg or propofol 0.75 mg/kg, and sufentanil 5-10 mcg. The analgesic drug will be administered 3 minutes before the sedative drug. When the patient is sufficiently sedated (Modified Observer's Assessment of Alertness/Sedation [MOAA/S]  $\leq 3$ ), the endoscopic examination will commence. If sedation is deemed inadequate or intubation fails, up to 5 supplemental doses (RT 2.5 mg) of intravenous bolus can be administered at 1-minute intervals within 15 minutes after the initial dose. If the initial dose and supplemental doses are insufficient to achieve adequate sedation for endoscopic insertion, the anesthesiologist will decide whether to administer a rescue sedative drug (propofol 0.75 mg/kg) at the start of the procedure. Once the procedure begins, to maintain an adequate level of sedation throughout the examination (MOAA/S score  $\leq 3$ ), supplemental doses of remimazolam will be administered to the patient at least 1-minute intervals (not exceeding 5 supplemental doses in total) based on the anesthesiologist's judgment. If these doses are insufficient to maintain appropriate sedation, a rescue sedative drug will be administered to complete the examination. If the use of rescue drugs raises safety concerns, the examination can be completed under general anesthesia with endotracheal intubation.

Throughout the procedure, the level of sedation will be assessed using the MOAA/S score. The anesthesiologist, who is blinded to the group assignment, will be responsible for the MOAA/S scoring. Before enrolling patients in this study, the evaluating physician will complete at least one training session to standardize the MOAA/S scoring. The MOAA/S score will be recorded at the

start of the initial drug administration, and frequently during the procedure until the patient is fully awake (three consecutive MOAA/S scores of 5).

## 5. Observation Indicators

### Primary Outcome:

The primary outcome is the incidence of respiratory depression (RD). Respiratory depression is defined as a respiratory rate  $< 8$  breaths per minute and/or  $SPO_2 < 90\%$  [7]. Respiratory rate will be monitored using end-tidal carbon dioxide monitoring. When a decrease in respiratory rate or oxygen saturation occurs, the anesthesiologist will need to assess the accuracy of the values to ensure normal readings. If airway obstruction due to tongue base retraction is relieved by airway maneuvers and the respiratory rate is above the assessment threshold, it will not be judged as respiratory depression, but the number of airway maneuvers will be recorded.

### Secondary Outcomes:

Secondary outcomes mainly include the incidence of intraoperative hypoxemia ( $SPO_2 < 90\%$ ,  $> 10s$ ), the number of minor airway maneuvers (such as jaw lift, patient repositioning, mask ventilation), the lowest  $SpO_2$ , the number of times the endoscope is removed due to persistent hypoxemia, and the success rate of sedation/analgesia (i. Completion of the entire endoscopic procedure; ii. No need for alternative and/or rescue sedatives; iii. Up to 5 supplemental doses administered within 15 minutes after the initial dose).

The examination time (from intubation to removal of the endoscope), sedation/analgesia time (from administration of analgesic drugs to full awakening), and awakening time (from administration of flumazenil to full awakening) will be recorded. The number of sedative drug supplements, the dose of sedative drugs used, and the dose of analgesic drugs used will be recorded. Vital signs (MAP, HR,  $SPO_2$ ) at different time points will be recorded. After the patient is fully awake, the occurrence of nausea and vomiting will be recorded. After the examination, the endoscopist's satisfaction will be recorded. The endoscopist will subjectively evaluate based on the operating conditions and whether the operation was interrupted, with a full mark of 10 points, 0-3 points for dissatisfaction, 4-7 points for relative satisfaction, and 8-10 points for satisfaction.

On the first postoperative day (postoperative Day 1, POD1), patient satisfaction will be recorded. Patients will subjectively evaluate based on their own feelings. Similarly, the full mark is 10 points,

with 0-3 points indicating dissatisfaction, 4-7 points indicating relative satisfaction, and 8-10 points indicating satisfaction. The occurrence of nausea and vomiting, itching, and urinary retention will be recorded.

#### IV. Adverse Events

During the entire study period, any AEs will be recorded, including but not limited to infectious diseases, hematological tests, systemic diseases, and injection site pain. As for AEs, hypotension is defined as a decrease of 30% or more in SBP from the baseline value and/or a mean arterial pressure < 60 mmHg; hypertension is defined as an increase of 30% or more in SBP from the baseline value; bradycardia is defined as HR < 60 beats per minute, > 10s; tachycardia is defined as HR > 100 beats per minute, > 10s; respiratory depression is defined as RR < 8 breaths per minute, SPO2 < 90%. Anesthesiologists will actively manage any abnormal conditions that occur in patients, including symptomatic treatment and active management of the underlying causes.

#### V. Statistical Analysis

##### 1. Sample Size Calculation

Based on the clinical practice of this research center and previously published studies [9-10], the incidence of respiratory depression during gastrointestinal endoscopy with remimazolam tosylate combined with propofol is referenced at 30%. If it is expected that remimazolam combined with etomidate can reduce the incidence of respiratory depression by 50%, the single-group sample size calculated using PASS software is 118 ( $\alpha=0.05$ ,  $\beta=0.8$ ). Considering a dropout rate of 5%, the single-group sample size is 124.

##### 2. Statistical Analysis

Statistical analysis will be performed using SPSS software. Continuous variables will be presented as mean  $\pm$  standard deviation (SD) or median M (P25, P75). The normality of continuous variable data will be assessed using the Kolmogorov-Smirnov test. Continuous variables that follow a normal distribution will be analyzed using the two-independent-samples t-test, while those that do not follow a normal distribution will be analyzed using the Mann-Whitney U test. Categorical variables will be expressed as counts and frequencies, and will be analyzed using the  $\chi^2$  test or Fisher's exact test. All statistical tests will be two-sided with a significance level set at  $P < 0.05$ , and 95% confidence intervals (95% CI) will be calculated.

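### The protocol's only tests for continuous data are unadjusted two-sample tests at P<0.05; applied to MAP, HR and SpO2 over time, this invites many uncontrolled tests and leaves the recorded baselines unused

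*Protocol*

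**What the plan says.** Three parts of the protocol bear on this.

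- **Section V.2, Statistical Analysis.** After a Kolmogorov-Smirnov check of normality, "Continuous variables that follow a normal distribution will be analyzed using the two-independent-samples t-test", and "those that do not follow a normal distribution will be analyzed using the Mann-Whitney U test". The error rate is the same throughout: "All statistical tests will be two-sided with a significance level set at" P<0.05. The section also promises 95% confidence intervals. It names no covariate, repeated-measures method or multiplicity control.
- **Section III.5, Secondary Outcomes.** MAP, HR and SpO2 "at different time points will be recorded". Their number and timing are not given. The lowest SpO2 is listed separately as an outcome of its own.
- **Section III.4, Study Interventions.** Before sedation, "monitoring devices will be connected to record baseline vital signs", including blood pressure and oxygen saturation.

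The protocol does not say in words that the vital signs will be tested separately at each time point.

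**The concern.** A two-sample test takes one value per patient. When the only rule for continuous data is a two-sample test and the data are serial readings, the straightforward result is a table of P values, one for each sign at each time point. Three things follow.

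1. **Multiplicity.** Each P value is read against 0.05, so the chance that some time point looks significant with no true difference grows with the number of time points.
2. **Precision.** The pre-sedation value of the same sign is available and usually predicts later values, but a two-sample test on the later value does not use it.
3. **Coherence.** Because the test depends on a normality check, the same sign may be compared by means at one time point and by ranks at the next. The profile then has no single quantity being estimated.

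The research background motivates the trial by the hemodynamic and respiratory effects of the sedatives. An isolated significant MAP or HR reading could therefore be given more weight than it can bear, while a real difference is estimated less precisely than the data allow.

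**Working it through.** **The plan's own figure.** The protocol states no error rate or power for the vital signs. Its one design calculation is for the binary primary outcome. The rate with propofol "is referenced at 30"%, etomidate "can reduce the incidence of respiratory depression by 50"% (so 15%), and "the single-group sample size calculated using PASS software is 118". With two-sided alpha 0.05 and power 0.80 (the printed beta of 0.8 read as power), the unpooled normal formula gives

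n = (1.960 + 0.842)² × (0.30×0.70 + 0.15×0.85) / 0.15² = 117.7, rounded up to 118.

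The figure is reproduced. It involves no continuous outcome; 118 is used below only as the number per group.

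**Step 1: false positives from repeated testing.** Assumptions, none of them in the protocol: k post-baseline time points, each tested at two-sided 0.05; equal correlation ρ between the k test statistics; no true difference; switching between tests ignored.

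With independent tests the chance of at least one false positive is 1 − 0.95^k. With correlation ρ it is 1 − P(all k statistics lie within ±1.96), for equicorrelated normal statistics.

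| k | ρ = 0 | ρ = 0.4 | ρ = 0.6 | ρ = 0.8 | ρ = 0.9 |
|---|---|---|---|---|---|
| 4 | 18.5% | 16.6% | 14.4% | 11.4% | 9.4% |
| 6 | 26.5% | 22.6% | 18.7% | 13.9% | 10.8% |
| 8 | 33.7% | 27.7% | 22.2% | 15.8% | 11.9% |

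These are per sign. For k from 4 to 8 and ρ from 0.4 to 0.9 the range is 9.4% to 27.7%.

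For three signs treated as mutually independent, the chance is 1 − (1 − per-sign value)³:

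- lowest: 1 − (1 − 0.0936)³ = 25.5% (k = 4, ρ = 0.9)
- highest: 1 − (1 − 0.2765)³ = 62.1% (k = 8, ρ = 0.4)
- middle case: 1 − (1 − 0.1868)³ = 46.2% (k = 6, ρ = 0.6)

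MAP, HR and SpO2 in one patient are unlikely to be independent, so the three-sign figures probably overstate the chance.

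**Step 2: what leaving out the baseline does.** In a randomized comparison the unadjusted t-test keeps its overall error rate. A simulation with 118 per group and baseline correlation 0.6 gave 4.97% rejections under no difference. The cost is variance: adjustment multiplies the residual variance by 1 − r², where r is the baseline correlation (assumed).

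For an assumed true difference of 0.3 SD at one time point and 118 per group, approximate power is Φ(0.3/√(1 − r²) × √(118/2) − 1.96).

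| r | 1 − r² | Variance reduction | Power |
|---|---|---|---|
| no adjustment | 1.00 | – | Φ(2.304 − 1.96) = 63% |
| 0.5 | 0.75 | 25% | Φ(2.661 − 1.96) = 76% |
| 0.7 | 0.51 | 49% | Φ(3.227 − 1.96) = 90% |

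**Step 3: one test per sign.** With a single 5% test per sign, the error is 5% per sign and 1 − 0.95³ = 14.3% over three if independent, in place of the ranges in Step 1.

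**The case against.** The strongest reply is that testing at every time point is an inference. The protocol says only that the readings are recorded. They might be described and not tested, or reduced to one summary value per patient, to which a two-sample test applies properly; the lowest SpO2 is such a summary. A statistical analysis plan, not seen here, could specify a longitudinal model. These are also secondary data, and hemodynamic events are defined separately under Adverse Events, where hypotension and hypertension are judged against baseline.

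Much of this stands. A reader might infer that the protocol commits itself to a test at each time point; it does not say so. It does fix the two-sample tests as its only methods for continuous variables, without exception, and it defines no summary value for MAP or HR. A longitudinal model would have to depart from that rule. The point is therefore a method fixed badly, not a detail left for later.

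Two other stronger readings are tempting and fail:

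- *Unused baselines inflate false positives.* They do not, averaged over randomization (Step 2). The inflation comes from the number of tests.
- *Ignoring within-patient correlation makes the tests invalid.* Each test at one time point uses one value per patient and is valid on its own. Positive correlation between time points lowers the chance of at least one false positive, as the table in Step 1 shows.

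It is also fair to object that a normal-error mixed model suits SpO2 poorly, since readings under supplemental oxygen sit near their ceiling, and that a single averaged arm effect could hide a brief difference after induction. Both points shape the fix.

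**Conclusion.** The concern holds in a limited form. As written, section V.2 most naturally leads to separate, unadjusted tests of MAP, HR and SpO2 at each time point. With 4 to 8 time points and between-test correlation 0.4 to 0.9, the chance of at least one false positive is about 9% to 28% per sign. Over three signs it is about 25% to 62% if they are independent, which is probably too high. Separately, the unused baselines cost precision: a variance reduction of 25% to 49% is forgone at baseline correlation 0.5 to 0.7. The number of time points and all the correlations are assumptions, so these are ranges and not estimates for this trial.

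A reader might infer that the main result is at risk. It is not: respiratory depression is a binary outcome, and neither its test nor the 118 per group is touched. The change is worth making because it uses data already being collected.

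**What to change.** Amend section V.2 as follows.

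- **MAP and HR.** Analyse each by one mixed model for repeated measures with arm, time, arm-by-time and the baseline value. Prespecify one test per sign: the joint test of arm and arm-by-time, so that a brief difference is not averaged away. Report time-point differences as estimates with 95% CI, without separate significance claims.
- **SpO2.** Use the lowest SpO2, already a secondary outcome, with a rank-based comparison, and report the time-point values descriptively.

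The cost is a little more analysis work, feasible in SPSS, which the protocol already names. No new data or patients are needed. Two drawbacks should be accepted openly: individual time points can no longer be declared significant, and a joint test has somewhat less power against a constant difference than a test of the average arm effect alone.

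### Read naturally, the median and Mann-Whitney rule would give no usable effect size for endoscope removals, and possibly for airway maneuvers; the share of patients with an event would.

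*Protocol*

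**What the plan says.** The Secondary Outcomes section of the protocol lists two event counts among the main secondary outcomes: "the number of minor airway maneuvers (such as jaw lift, patient repositioning, mask ventilation") and "the number of times the endoscope is removed due to persistent hypoxemia".

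Section V.2, Statistical Analysis, recognises two kinds of variable.

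- Continuous variables are checked for normality with the Kolmogorov-Smirnov test. If normal, they go to the t-test; of the rest it says that "those that do not follow a normal distribution will be analyzed using the Mann-Whitney U test". The summary is mean and SD, or median with P25 and P75.
- Categorical variables are given as counts and frequencies and compared by chi-square or Fisher.

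For all comparisons it adds that "95% confidence intervals (95% CI) will be calculated", without naming the quantity to be estimated.

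The Primary Outcome section is also relevant. Obstruction from the tongue base that a maneuver relieves, with the respiratory rate above the threshold, is not counted as respiratory depression; the number of maneuvers is recorded instead.

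**The concern.** A count of events per patient is numeric, so of the two routes the continuous one is the natural reading. A count that is zero in most patients fails a normality test and ends up as median (P25, P75) with Mann-Whitney. If fewer than a quarter of each arm has an event, all three printed numbers are 0 in both arms, whatever the P value.

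The promised confidence interval does not repair this. The interval conventionally paired with Mann-Whitney is for a location shift (Hodges-Lehmann), and with most pairs tied at zero it collapses to a point.

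What is at stake is interpretation, not the validity of a test. The maneuver count matters most, because it is where the protocol sends the obstructive events that it keeps out of the primary outcome. To judge whether fewer primary events mean less depression or more relieved obstruction, a reader needs the share of each arm that had a maneuver. A median and a rank P value do not show it.

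**Working it through.** **The plan's own figure.** The Sample Size section takes a rate in the propofol arm ("remimazolam tosylate combined with propofol is referenced at 30"%) and expects etomidate to "reduce the incidence of respiratory depression by 50"%, so 30% versus 15%. With two-sided alpha 0.05 and the printed beta of 0.8 read as power 0.80, the unpooled formula gives

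n = (0.30×0.70 + 0.15×0.85) × (1.960 + 0.842)² / 0.15² = 117.7, rounded up to 118 per arm.

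This matches the protocol, and 118 per arm is used below.

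**How rare are removals?** No rate is given. Removal needs persistent hypoxemia, and SpO2 below 90% is a component of respiratory depression, planned at 15 to 30%. Removals should therefore be well below 30% of the worse arm. This is an inference from a planning value, not a stated rate.

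**Worked example for removals (assumed): 12/118 versus 3/118 patients, one removal each.**

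1. Printed summary: 10.2% and 2.5% of patients have an event. Both are under 25%, so each arm reads 0 (0, 0).
2. Pairwise differences: 118×118 = 13,924 pairs. Of these, 12×115 = 1,380 equal +1, 106×3 = 318 equal −1, and the other 12,226 (88%) equal 0.
3. Mann-Whitney: U = 1,380 + 12,226/2 = 7,493, against an expected 13,924/2 = 6,962. The tie-corrected SD is 221.6, so z = 531/221.6 = 2.40 and P = 0.017.
4. Shift interval: without tie correction the SD is √(13,924×237/12) = 524.4. The lower limit is the difference ranked 6,962 − 1.96×524.4, about 5,934th; the upper limit is its mirror image, about 7,991st. Zeros occupy ranks 319 to 12,544, so the interval is 0 to 0. The tie-corrected SD gives the same.
5. Same data as proportions: 0.1017 − 0.0254 = 0.0763. SE = √(0.1017×0.8983/118 + 0.0254×0.9746/118) = 0.0314. The 95% CI is 0.0763 ± 0.0615, or 1.5 to 13.8 points. Chi-square P = 0.016; Fisher P = 0.030.

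**Range for airway maneuvers.** No rate is given, so it was varied. Simulation used 118 per arm and 1,000 trials per row; a patient with any event has 1 + Poisson(0.5) events (assumed). The columns describe trials with Mann-Whitney P<0.05; ranges are without and with tie correction of the interval.

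| Any event, worse vs better arm | Both medians 0 | Shift interval 0 to 0 |
|---|---|---|
| 10% vs 2% | 100% | 100% |
| 30% vs 15% | 100% | 99.9–100% |
| 40% vs 20% | 97.6% | 97.5–98.6% |
| 45% vs 25% | 82% | 92–95% |
| 49% vs 30% | 47% | 84–89% |
| 55% vs 35% | 5% | 63–70% |
| 60% vs 40% | 0.1% | 44–51% |

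**Quartiles.** In a similar simulation with 1 + Poisson(0.4), the printed median (P25, P75) differed between arms in about 96 to 97% of significant trials at 30% vs 15%, 94% at 40% vs 20%, 65% at 24% vs 12%, and none at 10% vs 2%. A typical line at 30% vs 15% is 0 (0, 1) versus 0 (0, 0). It shows a difference but not its size. With 35/118 versus 18/118 the risk difference is 14.4 points (95% CI 3.9 to 24.9).

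**The case against.** Four objections carry weight.

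- **Classification.** The protocol never calls these counts continuous, and they could be tabulated under the categorical rule. Such a choice can be left to a statistical analysis plan, which is not at hand. This stands as a limit: the point is about what the written rule does on its natural reading. The categorical route does not settle it either, since no grouping of the counts is fixed.
- **The interval.** No shift interval is named, and a difference in proportions or means would fit the same sentence. A reader might infer that the plan commits itself to an interval of 0 to 0 that contradicts its P value. The document does not support that; 0 to 0 is only what the conventional companion interval would show.
- **Rarity.** A reader might infer that both counts must be zero in most patients. That is reasonable for removals but unsupported for maneuvers. These include jaw lift and repositioning, and are recorded also in patients not counted as having respiratory depression, so they may exceed the 15 to 30% planned for that outcome. At 55% vs 35% the collapse is already much weaker.
- **Quartiles.** At moderate rates the printed summaries usually differ between arms, so it would be wrong to say that the summary always shows no difference.

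It is also tempting to argue that Mann-Whitney loses power and that a model for mean counts should be required. The simulations do not support that. With 30% vs 20% having any maneuver and mean extra maneuvers of 1.0 vs 0.4, a ratio of mean counts has about 84% power against 56 to 58%. With 30% vs 15% and equal repeats it has 67 to 69% against 78 to 79%. Neither is better throughout.

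**Conclusion.** The point holds as a cheap improvement in reporting, not as an error in a test. For endoscope removals the natural reading of the rule gives 0 (0, 0) in both arms and no usable effect size, even with P<0.05. This rests on removals being uncommon, which the planned 15 to 30% for respiratory depression makes likely. For airway maneuvers the loss is near certain if up to about 40% of the worse arm needs one, and fades beyond about half. Even where the quartiles differ, they do not show how many patients had obstruction relieved and so stayed out of the primary outcome.

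The tie-corrected Mann-Whitney P value remains valid, and the primary outcome and its sample size are untouched.

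**What to change.** Add one sentence to section V.2, or to the statistical analysis plan, before the data are analysed. For the number of airway maneuvers and the number of endoscope removals, the main summary is n (%) of patients with at least one event, compared by the chi-square or Fisher test already planned, with the risk difference and its 95% CI. Mann-Whitney on the count is kept as supportive. A ratio of mean counts with a robust 95% CI may be added descriptively.

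No new data are needed. The cost is one more analysis per outcome, and the at-least-one comparison ignores repeat events. Where the arms differ only in any versus none (30% vs 15%) it keeps its power, 79% against 78% for Mann-Whitney. Where they differ mainly in repeats (the 30% vs 20% scenario above) it falls to 44% against 58%, which is why the count analysis should stay alongside.

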#### 3. Randomization and Blinding

Researchers will use the website ([www.random.org](http://www.random.org)) to generate a block randomization scheme. All participants will be randomly assigned to receive remimazolam combined with etomidate or propofol for sedation/analgesia in a 1:1 ratio. The participants, anesthesiologists, endoscopists, and postoperative evaluators will be blinded to the group assignments. The anesthesiologist will be responsible for intraoperative and postoperative assessments. The group assignments will not be blinded to the anesthesia nursing staff who prepare the anesthetic drugs.

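### A respiratory-depression risk score (PRODIGY) is collected at baseline but has no role in the primary analysis: the planned unadjusted test is valid, but may forgo some precision

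*Protocol*

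**What the plan says.** Protocol section III.5 defines a binary primary endpoint: "The primary outcome is the incidence of respiratory depression (RD"). Section V.2 does not single this endpoint out. It gives one rule for all categorical data: "Categorical variables will be expressed as counts and frequencies, and will be analyzed using the" χ² or Fisher's exact test. It names no covariate, stratum or regression model. Section III.3 randomises in blocks, "for sedation/analgesia in a 1:1 ratio", and names no stratification factor.

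The baseline items in section III.4 end with "liver and kidney diseases), and PRODIGY score [7"]. Reference [7] is also the source cited in III.5 for the definition of respiratory depression. Its title in section VIII describes a study predicting opioid-induced respiratory depression on inpatient wards. All patients in this trial receive sufentanil (III.4). The protocol assigns the score no analytic purpose and gives no figure for its predictive strength.

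Section III.4 also indicates a mix of procedures: "patients will be positioned according to the type of examination".

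**The concern.** The trial takes its endpoint definition and a baseline risk score for that endpoint from the same source, then compares the arms without the score. When a baseline variable predicts a binary outcome, adjusting for it and averaging back to a marginal risk difference reduces the variance of the treatment estimate without adding patients. It also removes the part of the estimate that comes from chance differences between the arms in that variable.

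The planned size gives power of about 80% for a halving of risk, so there is little slack if the true effect is smaller. A covariate model chosen after unblinding would carry little weight, so the choice has to be written down beforehand.

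**Working it through.** **Inputs from the protocol.** The propofol-arm rate is "combined with propofol is referenced at 30" per cent and the etomidate combination "can reduce the incidence of respiratory depression by 50" per cent, so p₁ = 0.30 and p₂ = 0.15 (V.1). On testing: "All statistical tests will be two-sided with a significance level set at" 0.05 (V.2). Evaluable size is 118 per arm. V.1 writes β = 0.8, read here as power 0.80, because power 0.20 would need only 20 per arm.

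**Step 1: reproduce the plan's figure.** With unpooled variance,

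n = [p₁(1−p₁) + p₂(1−p₂)] × (1.960 + 0.842)² / (p₁−p₂)² = (0.21 + 0.1275) × 7.849 / 0.0225 = 117.7, so 118.

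This matches exactly. The pooled-variance formula gives 121. Power at 118 per arm is 80.1% (unpooled) or 79.2% (pooled). The stated size therefore rests on an unadjusted comparison of two proportions, and the planned test agrees with it.

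**Step 2: what adjustment would add.** The predictive strength of the score is not in the document, so it was varied. The assumptions were:
- One normally distributed baseline score x, with logit P(event) = a + g·arm + b·x.
- b set to 0, 0.36, 0.50, 0.75, 1.00 and 1.25, with intercepts calibrated to marginal rates of 0.30 and 0.15.
- 118 per arm and 6,000 simulated trials per setting.

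The unadjusted analysis was Pearson χ² without continuity correction. The adjusted analysis fitted the logistic model and took the mean over all patients of (predicted risk under etomidate − predicted risk under propofol), with an influence-function standard error.

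| Assumed AUC | Power, χ² | Power, adjusted | Gain (points) | Variance ratio | 118 × ratio |
|---|---|---|---|---|---|
| 0.50 | 80.5% | 80.6% | 0.1 | 1.007 | 118.8 |
| 0.60 | 80.8% | 82.1% | 1.3 | 0.985 | 116.3 |
| 0.64 | 80.4% | 82.0% | 1.6 | 0.966 | 113.9 |
| 0.70 | 81.0% | 84.0% | 3.0 | 0.927 | 109.4 |
| 0.74 | 80.4% | 85.6% | 5.2 | 0.877 | 103.4 |
| 0.78 | 80.3% | 87.9% | 7.6 | 0.821 | 96.9 |

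The Monte Carlo standard error of each power figure is √(0.8 × 0.2 / 6000) = 0.5 point. The last column is the size per arm at which adjustment would give the precision of 118 unadjusted. At AUC 0.70 that is about 9 patients per arm fewer; at 0.60 it is about 2.

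**Step 3: validity.** With both arms at 30%, type I error was 5.0 to 5.5% for χ² and 5.2 to 5.6% for the adjusted analysis (Monte Carlo standard error about 0.3 point). Both are close to nominal.

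**Step 4: chance imbalance.** The standard error of the difference in mean score, in SD units, is √(2/118) = 0.130. The chance of an imbalance above 0.2 SD is therefore P(|Z| > 0.2/0.130 = 1.54), about 12%. For examination type at an assumed 50% prevalence, the 95% range is ±1.96 × √(0.25 × 2/118) = ±0.128, about 13 percentage points. The unadjusted test's error rate already allows for imbalances of this kind.

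**Step 5: capacity for covariates.** Expected events are 118 × (0.30 + 0.15) = 53, ample for a model with arm and one or two covariates.

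**The case against.** The strongest reply is that nothing here is broken. An unadjusted comparison of two proportions is a legitimate primary analysis in a 1:1 randomised trial. It holds its error rate and is the analysis the sample size was built on. Covariate choice is often left to the SAP, which was not available, and V.2 does not forbid an adjusted analysis. Its sentence on categorical data is general and does not name the primary outcome.

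Most of this stands and limits the point. What remains is that V.2 states a method, does not defer to another document, and offers no other method for a binary primary outcome. A better use of data already being collected can therefore be recommended. An SAP that adjusts would have to be reconciled with V.2.

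A reader might go further in three ways that the document does not support:
- **That precision is certainly lost.** No predictive strength is given, and the cited source concerns inpatient wards, not sedated endoscopy with remimazolam plus etomidate or propofol. The gain could be nil.
- **That chance imbalance undermines the χ² test.** It does not: the test's error rate covers it. Adjustment improves the estimate given the imbalance that occurs.
- **That examination type goes unrecorded and threatens the comparison.** The baseline list is introduced as inclusive, not exhaustive. No section shows that examination type predicts the outcome, and the 50% prevalence in step 4 is an assumption.

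**Conclusion.** The point holds as a low-cost improvement, not as an error or contradiction. The only stated analysis of the primary outcome makes no use of a respiratory-depression risk score collected at baseline. Under the protocol's own rates and 118 per arm, prespecified adjustment would leave power essentially unchanged if the score does not predict the outcome here. It would add 1 to 2 points at AUC 0.60 to 0.64, 3 at 0.70 and 5 at 0.74. The 7.6 points at 0.78 are the top of the range examined and should not be expected.

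These figures assume a single normally distributed score with a linear effect on the logit, the planned 30% and 15% rates, and 118 patients analysed per arm. The AUC is an assumption throughout. The conclusion that adjustment costs almost nothing does not depend on which AUC in this range is true.

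**What to change.** In Protocol section V.2, and in the SAP if there is one, prespecify before unblinding:
- **Primary estimate:** the marginal risk difference in respiratory depression with a 95% CI, from a logistic model with arm and PRODIGY score, standardised over all randomised patients with an outcome, with a robust or bootstrap standard error.
- **Target:** state that the marginal risk difference is the quantity of interest. The model's conditional odds ratio is a different quantity from the contrast used for the sample size.
- **Supportive analysis:** the unadjusted χ² test as now planned.
- **Optional:** examination type as a second covariate, provided that it is recorded at baseline.

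The sample size need not change. The cost is a small amount of analysis work and a short edit to V.2, plus one baseline field if examination type is wanted and not already captured.
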